## Methods

### Study design

This is a protocol for a randomized, controlled blind, longitudinal clinical trial, as shown in
Figure 1. This project will be carried out at Nove de Julho University in São Paulo, Brazil.

**Figure 1. f1:**
[figure not shown]
Study enrollment schedule, outcomes, and interventions. tDCS. transcranial direct current stimulation.

### Eligibility criteria

The inclusion criteria are people between 60 and 80 years old, of both genders, able to stand or walk without the aid of auxiliary devices, with reduced balance (score ≤25 points) evaluated using the Mini-BESTest
^19^. Exclusion criteria are cognitive impairment (scores ≤14 points) corrected for education, measured by the Mini-Mental State Examination (MMSE)
^20^, presence of lower limb fractures or amputations, neurological diseases, cardiovascular diseases that limit the performance of exercises, untreated acute and chronic respiratory diseases and the presence of pain that limits movement; the presence of contraindications to the use of tDCS.

### Consent to participate

The informed consent form will be explained to all participants. The volunteers who participate in this study, must sign the form (supplementary file 1), which guarantees the secrecy and confidentiality of data, free access to the final data, explanations of any kind related to the study and possible compensation for those that suffer from participation in the study.

### Ethics approval

The protocol was approved in May 2018 by Human Research Ethics Committee of the University Nove de Julho, São Paulo, Brazil (Opinion number 2.962.837), and Brazilian Clinical Trials Registry (ReBec), number: U1111-1213-4266, in accordance with Resolution 466/12 of the National Health Council of Brazil.

### Recruitment and allocation

Participants in this study will be community elders elected according to the criteria established for allocation. They will be randomized into 3 groups:

Group 1: Control Group (Video game balance training);

Group 2: Anodal group (Video game balance training associated with anodal tDCS);

Group 3: Sham Group (Video game balance training associated with sham tDCS).

A researcher not involved in evaluations or training will be responsible for allocating participants via
www.randomization.com.

### Sample size

The sample size was obtained using
G*Power 3.0.10 software, based on the outcomes from a pilot study. The calculation was carried out by the two-way repeated measures analysis of variance (ANOVA), considering the mean value (before and after training, and 30-day follow-up) for the control groups (25.46) active (27.46) and sham (24.66) and the pooled standard deviation (SD
_pooled_) (2.89), with α = 0.05, β = 0.2 (80% of power) and the effect size of 0.40. A total of 15 individuals were determined to be required for each group (total sample: 45 individuals). Considering possible dropouts and to ensure a sample size that will demonstrate the effect of the intervention, the sample will be expanded by 25%, resulting in 19 individuals in each group, thus totalling 54 participants.

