### Primary outcomes

***Postural balance***. The assessment of postural balance will be performed by the Mini BESTest Scale, which consists of 14 functional tasks, such as sitting and getting up from a chair, standing up, balancing on tiptoes, and on one foot, overcoming walking obstacles, and double activities task
^21^.

Performance can range from 0 to 28 points. Each test can be performed for up to three attempts and the best result will be obtained. If adaptations are necessary to accomplish this, a point will be deducted from the maximum score obtained. This is a very reliable instrument, with an intraclass correlation (ICC) of 0.84)
^22^.

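### The active-arm planning mean of 27.46, if it is a three-visit Mini-BESTest mean, exceeds the 27.00 that the trial's own entry limit and scale maximum allow, so f = 0.40 and 80% power are unsupported for the people to be enrolled

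*Protocol article*

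**What the plan says.** The Sample size section of the protocol article takes its inputs from earlier data, "based on the outcomes from a pilot study". It gives one mean per group and describes it as covering all three assessments: "considering the mean value (before and after training, and 30-day follow-up) for the control groups (25.46) active (27.46) and sham (24.66"). The pooled SD is 2.89, and the calculation runs "with α = 0.05, β = 0.2 (80% of power) and the effect size of 0.40". The result is 15 evaluable participants per group: "A total of 15 individuals were determined to be required for each group (total sample: 45 individuals"). The named method is a two-way repeated measures ANOVA. The section does not say which outcome the means belong to, which entry criteria the pilot used, or what correlation between visits was assumed.

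Two other sections limit what a Mini-BESTest mean can be in this trial. Eligibility criteria admits people "with reduced balance (score ≤25 points) evaluated using the Mini-BESTest". Primary outcomes says of the same scale: "Performance can range from 0 to 28 points".

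**The concern.** The Mini-BESTest is the only primary outcome, and the three planning values lie within its range, so it is natural to read them as Mini-BESTest scores. On that reading the entry limit fixes the highest possible baseline and the scale fixes the highest possible later score. The active-arm planning mean lies above what the two limits together allow.

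The three means and the SD are the only stated source of the effect size, and the effect size is the only stated source of the group size. If the means come from people whom this trial would not enrol, the claim of 80% power does not carry over to the people it will enrol. Readers of a null result would then not know what difference the trial could have detected.

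**Working it through.** **Inputs.** From Sample size: means 25.46 (control), 27.46 (active), 24.66 (sham); SD 2.89; α = 0.05; f = 0.40; N = 45. From Eligibility criteria: baseline at most 25. From Primary outcomes: maximum 28. From Outcome assessments: three visits. Not stated: the correlation ρ between visits. I take 0.5 as the reference and show 0 to 0.84.

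**Step 1: reproduce the stated effect size.**
- Grand mean = (25.46 + 27.46 + 24.66)/3 = 25.86.
- Squared deviations: 0.16, 2.56, 1.44; their mean is 1.387, with square root 1.178.
- f = 1.178/2.89 = 0.4075, in line with the stated 0.40.

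**Step 2: reproduce the stated sample size.** For the between-group test over m = 3 visits, λ = N f² m / (1 + (m − 1)ρ), with 2 and N − 3 degrees of freedom.
- At f = 0.40, N = 45, ρ = 0.5: λ = 45 × 0.16 × 3/2 = 10.8, power 81.7%. Going up in steps of three, 45 is the first total to reach 80%.
- The group-by-time interaction would need 18 and a one-way ANOVA 66, both at f = 0.40 (the interaction at ρ = 0.5). The between-group test averaged over three visits is therefore the version that fits, which agrees with the section's description of the means.

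**Step 3: compare the active mean with the trial's limits.**
- Largest three-visit mean = (25 + 28 + 28)/3 = 27.00, reached only if every participant scores exactly 25, 28 and 28. The planning value is 27.46.
- With perfect scores at both later visits, the baseline mean would have to be at least 3 × 27.46 − 56 = 26.38, above the entry limit.
- With a baseline mean of 25, the later-visit mean would have to be (3 × 27.46 − 25)/2 = 28.69, off the scale.

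**Step 4: illustrate the sensitivity.** Lower the active mean to 27.00 and hold the other two means and the SD as stated. The grand mean is 25.707, the root mean squared deviation is 0.971, and f = 0.971/2.89 = 0.336.

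| ρ (assumed) | Power at N = 45, f = 0.40 | Power at N = 45, f = 0.336 |
|---|---|---|
| 0 | 99% | 93% |
| 0.5 | 82% | 66% |
| 0.84 | 69% | 53% |

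The first power column shows that even the stated effect size reaches 80% only if the unstated correlation is not much above 0.5.

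**The case against.** **The calculation is internally sound.** This stands. The stated f and N follow from the stated inputs, so a reader who infers that the figures have no basis goes too far. The defect is that the inputs do not fit the population.

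**f depends on differences, not levels.** This stands as arithmetic. Lowering all three means by 1 point gives 24.46, 26.46 and 23.66, keeps f at 0.4075 and brings the active mean under 27.00. So the infeasible level does not prove that 0.40 is unattainable. But a common shift is a new assumption, not the pilot result. On the three-visit reading, the active pilot arm started at 26.38 or higher. If control and sham did not worsen on average (an assumption), they started no higher than 25.46 and 24.66. At least 26.38 − 25.46 = 0.92 of the 2.00-point gap to control, and 26.38 − 24.66 = 1.72 of the 2.80-point gap to sham, would then have been present before training.

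**The illustration holds the SD fixed.** This also stands. A mean of exactly 27.00 leaves the active arm with no variance. If only control and sham keep SD 2.89, the pooled SD is 2.89 × √(2/3) = 2.36, f = 0.971/2.36 = 0.41, and power at N = 45 is 84% (ρ = 0.5). A reader might infer from the 66% that true power is below 80%; the documents do not establish that.

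**Other readings remove the impossibility.** In part. If the outcome is not the Mini-BESTest, the limits of 25 and 28 do not apply, but the section then gives no sample-size basis for the primary outcome. If 27.46 is a post-training value, it is possible, but the description of the means is wrong. A pilot with wider entry criteria raises the question of whether its effect carries over to this trial. None of these shows that the calculation is invalid; each leaves something to be clarified.

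**Conclusion.** The point holds in limited form. Read as written, and taking the outcome to be the Mini-BESTest, the active-arm planning mean is 0.46 points above the most that eligible participants could average over three visits. The pilot means therefore do not describe the people to be enrolled, and f = 0.40 with 80% power is unsupported for them.

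The conclusion rests on two readings: that the outcome is the Mini-BESTest, which is inferred, and that each mean covers all three visits, which the text states and the reproduction of N = 45 supports at an assumed correlation of 0.5. The document does not show what the true power is. The range of 53% to 93% illustrates sensitivity to one change in one mean and to the unstated correlation; it is not an estimate.

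**What to change.** Revise the Sample size section to:

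- name the outcome and the visit or visits behind the three means;
- recompute the effect and the SD from pilot participants with a baseline Mini-BESTest of 25 or below, using the group differences at post-training and at 30 days;
- state the assumed correlation between visits;
- replace the claim of 80% power at effect size 0.40 with the power, or the detectable difference, that the planned group size delivers.

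The cost is a recalculation and a rewritten paragraph. The stated power may become less favourable. No added enrolment is required, and the design, the outcome and the analysis stay as they are.

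### The enrolment target contradicts itself: three groups of 19 make 57, but the stated total is 54, which is 18 per group and a 20% expansion, not 25%

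*Protocol article*

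**What the plan says.** The Recruitment and allocation section of the protocol article fixes the number of arms: "They will be randomized into 3 groups" (control, anodal and sham). The Sample size section gives the requirement before any allowance for loss: "A total of 15 individuals were determined to be required for each group (total sample: 45 individuals"). It then adds a margin for possible dropouts: "the sample will be expanded by 25%, resulting in 19 individuals in each group, thus totalling 54 participants".

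The calculation behind the 45 is described as a two-way repeated measures ANOVA "with α = 0.05, β = 0.2 (80% of power) and the effect size of 0.40". The article states neither an expected dropout rate nor a correlation between the repeated measurements, and no other section gives an enrolment total.

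**The concern.** One sentence gives three figures that should follow from one another: a 25% expansion, 19 per group and 54 in total. The first two agree; the third agrees with neither. Because the sentence says 19 in each group, unequal allocation cannot explain the difference.

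The enrolment total decides when recruitment stops and how long the allocation list must be. With two targets in the text, stopping at 54 can be read as three short and continuing to 57 as over-enrolment. The margin is also there to keep 45 analysable participants, and the smaller total tolerates fewer losses than the stated expansion does.

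**Working it through.** **Inputs from the protocol article.** Three groups (Recruitment and allocation). From Sample size: 15 per group and 45 in total; expansion 25%; 19 per group and 54 in total after expansion; alpha 0.05; power 80%; effect size f = 0.40; group means 25.46, 27.46 and 24.66; pooled SD 2.89.

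**Assumptions, not in the article.** The power calculation uses the between-factors test and a correlation ρ between repeated measures of 0.5, with 0.3 and 0.7 as a range. Loss rates of 20% and 25% are used for illustration.

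**1. The effect size and the 45.**
- Mean of the three group means: (25.46 + 27.46 + 24.66)/3 = 25.86.
- Deviations: −0.40, 1.60, −1.20. Mean square: (0.16 + 2.56 + 1.44)/3 = 1.387. Square root: 1.178.
- f = 1.178/2.89 = 0.407, in line with the stated 0.40.
- Non-centrality with m = 3 measurements: λ = N f² m / (1 + (m − 1)ρ). At N = 45, f = 0.40 and ρ = 0.5, λ = 45 × 0.16 × 3 / 2 = 10.8 on 2 and 42 degrees of freedom, and power is 81.7%.
- At N = 42 under the same assumptions, λ = 10.08 and power is 78.6%. So 45 is the smallest equal-group total that reaches 80%, and the base requirement reproduces under these assumptions.

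**2. The expansion.**
- Per group: 15 × 1.25 = 18.75, rounded up to 19. This reproduces.
- Total from the per-group figure: 3 × 19 = 57.
- Total from the base: 45 × 1.25 = 56.25, rounded up to 57.
- Stated total: 54. Working back, 54/3 = 18 per group and 54/45 = 1.20, a 20% expansion.
- Reading the 25% as a dropout rate does not give 54 either: 45/(1 − 0.25) = 60.

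**3. What each total tolerates.** The largest loss that still leaves 45 is 1 − 45/N.
- 54: 1 − 45/54 = 16.7%, or 9 people.
- 57: 1 − 45/57 = 21.1%, or 12 people.

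| Loss | Left of 54 | Left of 57 | Enrolment needed for 45 |
|---|---|---|---|
| 16.7% | 45.0 | 47.5 | 54 |
| 20% | 43.2 | 45.6 | 57 |
| 25% | 40.5 | 42.75 | 60 |

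The 20% row is the algebraic inverse of a 25% expansion: 1 − 1/1.25 = 0.20.

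**4. Effect on power** (between-factors test, f = 0.40):

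| Assumed ρ | 43 completers | 45 completers | Difference (points) |
|---|---|---|---|
| 0.3 | 88.2% | 89.8% | 1.6 |
| 0.5 | 79.7% | 81.7% | 2.0 |
| 0.7 | 71.6% | 73.8% | 2.2 |

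With f = 0.407 and ρ = 0.5, power at 43 completers is about 81%.

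**The case against.** A reader might infer that a total of 54 fails to protect the required 45. The protocol does not support that as a flat statement. It gives no dropout rate, and 54 keeps 45 completers as long as no more than 9 people are lost. The 20% loss is only the inverse of the stated expansion, not a planning figure of the authors. They may equally have expected 25% dropout, and then 57 would fail as well. This objection stands, so the shortfall can only be stated conditionally.

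A reader might also infer that stopping at 54 takes the trial below 80% power. That rests on an assumed correlation and on the choice of the between-factors test. Small changes in either input move the result across the 80% line: at the effect size that the protocol's own means and SD give, 43 completers still reach about 81%. What is stable across the range is the difference of about 2 points. This objection stands too.

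Finally, the document does not prove which figure is the slip. The 25% and the 19 support each other, which makes 57 the likelier intention, but 54 could be the number that the authors meant to recruit. None of these objections removes the contradiction, which rests on multiplication alone.

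**Conclusion.** The point holds as an internal contradiction in the enrolment target. The figures "resulting in 19 individuals in each group" and "thus totalling 54 participants" cannot both be right for three groups; they differ by three participants, or one per group. This part needs no assumption.

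The consequence is conditional and modest. The smaller total has a tolerance of 16.7% loss instead of about 21%, so it falls short of 45 where the larger would not only when losses lie between those two rates. The cost in power at an assumed 20% loss is about 2 points. The reason to correct it is that the recruitment target is ambiguous as written, not that the trial would be materially underpowered.

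**What to change.** Reconcile the expansion, the per-group size and the total in the Sample size section, in one of two ways:

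- correct the total to 57, which matches the stated 19 per group and 25% expansion; or
- if 54 is the true target, state 18 per group and a 20% expansion.

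In either case, state the dropout rate that the chosen total absorbs: up to about 21% for 57, or 16.7% for 54. If the authors actually expect 25% dropout, neither total keeps 45 and 60 would be needed.

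The cost of the first option is one corrected figure and at most three participants, whom the stated 19 per group already implies. The second costs two corrected figures and no participants. The dropout rate adds a sentence, and the allocation list should be checked against whichever total is kept.

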### Outcome assessments

All evaluations will be carried out on three occasions: pre-intervention, after eight treatment sessions and 30 days after the end of the training (follow-up). The training will be held twice a week, for 4 weeks, totalling 8 sessions.

### Primary outcomes

***Postural balance***. The assessment of postural balance will be performed by the Mini BESTest Scale, which consists of 14 functional tasks, such as sitting and getting up from a chair, standing up, balancing on tiptoes, and on one foot, overcoming walking obstacles, and double activities task
^21^.

Performance can range from 0 to 28 points. Each test can be performed for up to three attempts and the best result will be obtained. If adaptations are necessary to accomplish this, a point will be deducted from the maximum score obtained. This is a very reliable instrument, with an intraclass correlation (ICC) of 0.84)
^22^.

### Secondary outcome

***Static postural balance***. Posturography data will be collected using the Wii Balance Board (Nintendo, Kyoto, Japan), which is a validated instrument for posturography evaluation
^23^. The software for postural assessment is available at
http://www.rehabtools.org/sway.html.

The evaluation protocol will be performed in two conditions, standing with eyes open and then with eyes closed. These two postures are reliable for measuring body sway, with eyes open with (ICC: 0.77) and with eyes closed (ICC: 0.89)
^23^.

To standardize the collections, the initial position of the feet on the evaluation platform will be marked and the same measurement repeated in all evaluations. The tests will last 1 minute, the initial 30 seconds will be to establish the patient’s suitability and the final 30 seconds will be to collect the posturography data.

***Quality of life (QOL)***. QOL will be measured by the World Health Organization’s Quality of Life Instrument, Bref version
^24^, which is composed of 26 questions, scored from 1 to 5, with the worst and the best scores being 26 and 130, respectively. In studies with the older people, it showed a high degree of reliability to mediate quality of life in the domain of physical capacity (0.89), psychological well-being (0.95), social relationships (0.81), and the environment (0,93).

### Potential confusion factors

***Symptoms of depression***. The symptoms of depression will be evaluated and classified according to severity, using the Beck Depression Inventory (BDI), a questionnaire composed of 21 questions, which can be self-applied. Scores from 0 to 10 indicate an absence of depression; 11 to 18 indicate mild depression; 19 to 29 indicate moderate depression and 30 to 63 is considered severe depression
^25^. In studies with the older people, the BDI score shows a degree of reliability r = 0.78
^26^. Subsequently, it will be assessed whether the emotional state interfered with the results.

### The use of medication

The information related to continuous-use medication will be monitored through the application of a questionnaire prepared by the author. Such information will be used to characterize the sample.

### Intervention procedures

***Video game Balance training***. The balance training sessions will be performed using only the video games in group 1 (control), group 2 will be the balance training with the video games associated with the anodal tDCS and group 3 will be the balance training with the video games associated with the sham tDCS. In this study, a control group was added that performed the same training as the other groups. However, using only the video game. The justification for this was to verify if only the balance training with video game is efficient and if the tDCS additional can potentiate the training results, making the outcomes more effective. The sham group was used to verify if the response to balance training with video game, can be influenced by some placebo effect.

Video game training will be carried out with the Nintendo Wii and Wii Fit Plus, placed in a slide projector to enlarge the image. The sequence of games will always be the same, and the participant should play an average of 5 to 7 minutes each game, passing the stage according to their learning.

The sessions will be held twice a week, for four weeks, totalling eight sessions. Each session will last 20 minutes. The selected games are table tilt, penguin slide and ski slalom, which will be performed standing on the Wii Board Balance and require movements that stimulate balance, such as the anterior, posterior and lateral tilt of the body, without moving (
Figure 1).

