18^, therefore, further studies are necessary to verify the benefit of tCDS in association with other therapies. For that reason, the primary objective of this study is to assess whether tDCS can enhance and prolong the effects of videogame training on improving postural balance in the older people. Secondarily, check if there is a relationship between the response to training and the quality of life. This study hypothesizes that the association of tDCS with virtual reality therapy is more effective in improving balance in the older people than therapy with videogames alone, and that the addition of tDCS will prolong the effects of balance training.

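### The games-only arm is partly justified as verifying that video-game training works by itself, but every arm trains, so no randomised comparison can show this

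*Protocol article*

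**What the plan says.** The Recruitment and allocation section of the protocol article defines three arms. The first is listed as "Group 1: Control Group (Video game balance training". The other two give the same game sessions, one with active stimulation and one with the sham procedure.

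Intervention procedures confirms that "a control group was added that performed the same training as the other groups". It then gives the reason for that arm: "The justification for this was to verify if only the balance training with video game is efficient". The same sentence adds a second purpose, to see whether tDCS strengthens the training result. The third arm has its own purpose: "The sham group was used to verify if the response to balance training with video game, can be influenced by some placebo effect".

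The hypothesis in the Introduction is about the add-on only: "the association of tDCS with virtual reality therapy is more effective in improving balance in the older people than therapy with videogames alone".

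Eligibility criteria admits people "with reduced balance (score ≤25 points) evaluated using the Mini-BESTest". The Mini-BESTest is also the primary outcome, scored 0 to 28 with a stated ICC of 0.84, and is measured on three occasions. The Blinding section says that participants in the games-only arm are not blinded. Statistical analysis plans a two-way repeated-measures ANOVA over three groups and three times, with Friedman's test as the nonparametric alternative.

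**The concern.** Showing that a training programme works needs a comparison with people who did not train, or who did something else. This trial has no such arm. The games-only arm is a control for tDCS, not for training, so the first of its two stated purposes has no randomised comparison behind it.

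What remains is an uncontrolled before-after change. Three features of the design can raise that change when training does nothing. Low scorers on the outcome scale are selected and tend to score higher on retest. The same test is given three times. Participants in group 1 know what they receive.

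At stake is one possible conclusion. If scores rise in group 1, or the ANOVA shows a time effect, the current wording invites the statement that the games by themselves have been verified to improve balance. No analysis plan can repair this, because the missing element is a comparator.

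**Working it through.** **1. What each contrast estimates**

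| Contrast | Differs in | Estimates |
|---|---|---|
| Active tDCS minus sham | real versus sham current | effect of the current, added to training |
| Active tDCS minus games-only | whole tDCS procedure | tDCS plus its placebo component, added to training |
| Sham minus games-only | sham procedure | placebo component, added to training |

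Training is common to both sides of every row and drops out. The change over time does contain training, but no randomised comparison separates it from other causes of change.

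**2. The plan's own figure**

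The sample size rests on means of 25.46, 27.46 and 24.66 and a pooled SD of 2.89. The grand mean is 77.58/3 = 25.86 and the deviations are -0.40, 1.60 and -1.20. So f = sqrt((0.16 + 2.56 + 1.44)/3)/2.89 = 1.178/2.89 = 0.407, which agrees with the stated 0.40. With f = 0.40, alpha 0.05, three measurements and an assumed correlation of 0.5, the between-groups test needs 45 participants (power 0.817). The stated 15 per group is reproduced. It is driven entirely by differences between three trained groups and carries no information on training against no training.

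**3. How large an artefact could be**

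From the documents: cut-off 25, SD 2.89, ICC 0.84, n = 15 per arm.

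Assumptions: 2.89 is the SD of the screened population (it is given as the pilot's pooled SD); that population is roughly normal with mean 24 to 26; the screening score serves as the pre-intervention score; the between-visit correlation rho equals the ICC.

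Expected rise with no training effect = (1 - rho) × SD × phi(z)/Phi(z), where z = (25 - mean)/SD. Here (1 - 0.84) × 2.89 = 0.4624.

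| Mean | z | phi/Phi | Expected rise |
|---|---|---|---|
| 24 | 0.346 | 0.3758/0.6353 = 0.591 | 0.27 |
| 25 | 0 | 0.3989/0.5000 = 0.798 | 0.37 |
| 26 | -0.346 | 0.3758/0.3647 = 1.030 | 0.48 |

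A variant with a continuity-corrected cut of 25.5, means of 23 to 26 and SDs of 2.89 to 4.0 gives 0.2 to 0.6 points at the same reliability.

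**4. What a one-arm test would do with it**

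Baseline scores were simulated from the distribution truncated at 25. Retest scores were simulated with correlation 0.84 and no training effect, and 15 participants were compared by a paired t-test. The test falls in the upper 2.5% tail in about 9%, 13% and 19% of trials for means of 24, 25 and 26. Capping retest scores at the 28-point maximum hardly changes these rates.

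**5. Sensitivity**

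At rho = 0.7 the rise is 0.51 to 0.89 points, and at rho = 0.5 it is 0.85 to 1.49. If baseline is measured again after screening, the rise is smaller. Retest familiarity and expectation would come on top, and the documents do not allow them to be sized.

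**The case against.** The strongest reply is that the disputed words are half of one sentence of rationale. The other half asks whether tDCS adds to training, and group 1 is a valid comparator for that. The objective and hypothesis in the Introduction concern the add-on only. Statistical analysis specifies no paired test in group 1 and draws no efficacy conclusion from the time effect. The clause might also mean no more than whether games are enough or tDCS adds something.

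Much of this stands, and it rules out several stronger readings that a reader might infer:

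- *The trial's main comparison is biased.* It is not. Regression to the mean and retest familiarity are expected equally in all randomised arms and cancel from differences between them. For the same reason the artefact should not be measured against the 2.0-point active-control difference used for planning (27.46 - 25.46).
- *The before-after change will certainly overstate the effect.* Upward is the expected direction, but the documents do not establish it as a certainty. They do not say whether the screening score is also the baseline.
- *The artefact exceeds a point, with false improvement in about half of trials.* That needs a correlation near 0.5, and the only reliability the documents give is 0.84.
- *The protocol plans a misleading test.* It plans no such test. The 9% to 19% describes what would happen if one were used.

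The reply does not remove the point. On its natural reading the clause promises to verify that training by itself works. If only a before-after reading was meant, an uncontrolled change cannot verify that, and the text gives no caveat.

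**Conclusion.** The point holds in a limited form. One stated purpose of the games-only arm cannot be met by this design, whatever the size of any artefact, because no randomised contrast isolates training.

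The numerical part is illustrative: about 0.3 to 0.5 Mini-BESTest points from regression to the mean, under the assumptions listed in the working. It shows that a modest rise over time is possible with no training effect.

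The primary question is untouched, and no outcome, sample size or planned contrast has to change. The lack of blinding in group 1 is a reason to treat active versus games-only as a supporting comparison. Severity is minor to moderate: the defect limits what may be concluded, not whether the trial can answer its main question.

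**What to change.** In Intervention procedures:

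1. Remove the claim that group 1 verifies the efficacy of training by itself.
2. State that within-arm changes and the time main effect are descriptive, reported as mean change with a 95% confidence interval, with no conclusion on efficacy.
3. Give group 1 the roles that randomisation supports: comparator for sham, to estimate the placebo effect of the tDCS procedure, and comparator for active tDCS, as a supporting comparison.

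Suitable wording would be: *The games-only group serves as comparator for the sham and active tDCS groups. Because all groups train, changes over time are described without inference about the efficacy of training.*

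The cost is one or two sentences and the loss of one claim. No arm, visit, measurement or participant is added. Trial status says that data collection is under way, but the change concerns wording and reporting only and can still be made.
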